# The efficacy of temozolomide combined with levetiracetam for glioblastoma (GBM) after surgery: a study protocol for a double-blinded and randomized controlled trial

**DOI:** 10.1186/s13063-022-06168-1

**Published:** 2022-03-28

**Keywords:** Glioblastoma (GBM), Temozolomide, Levetiracetam, Chemotherapy, Clinical trial

## Abstract

**Background:**

Temozolomide is applied as the standard chemotherapy agent in patients with glioblastoma (GBM) after surgery. However, the benefit of this treatment for patients is limited by the invasive growth of gliomas and drug resistance. There are indications from fundamental experimental and retrospective studies that levetiracetam has the potential to improve the survival rate of patients with GBM. However, it has yet to be determined whether the combination of temozolomide and levetiracetam is more effective than standard temozolomide chemotherapy. Therefore, we designed a randomized clinical trial to investigate the therapeutic effect of the new combined regime for treating GBM.

**Methods/design:**

This is a double-blind and randomized clinical trial conducted in a single center. One hundred forty-two patients will be recruited and screened for the inclusion and exclusion criteria. Then, eligible participants will be randomly assigned to an experimental group or a control group in a 1:1 ratio. Based on the administration of radiation therapy (RT), participants in the experimental group will be prescribed levetiracetam plus temozolomide chemotherapy for 34 weeks while participants in the control group will receive placebo tablets plus temozolomide for the same duration. A 3-year follow-up will be conducted on all patients after intervention. Accordingly, the primary outcome will be progression-free survival (PFS). The secondary endpoints include overall survival (OS), the Karnofsky Performance Status (KPS), the objective response rate (ORR), and adverse event incidence.

**Discussion:**

It is expected that the results of this trial will provide high-level evidence regarding the clinical benefits of levetiracetam and temozolomide combined in the treatment of GBM.

**Trial registration:**

Chinese Clinical Trial Registry, ChiCTR2100049941. Registered on 14 August 2021

**Supplementary Information:**

The online version contains supplementary material available at 10.1186/s13063-022-06168-1.

## Background

Glioblastoma (GBM) accounts for up to 60% of all primary malignant brain tumors in adults [1] and it is also known as astrocytoma grade IV according to 2016 WHO classification [2]. GBM is the most aggressive and lethal form of primary astrocytoma, due to the highly infiltrative and heterogeneous nature of the glioma cells. Currently, the standard of care for GBM patients consists of maximal surgical resection plus adjuvant chemotherapy and radiation therapy (RT) [3]. Despite multimodal treatment, the prognosis of patients with GBM is still extremely poor with a 5-year overall survival rate of less than 5% post-diagnosis [4]; 2–3% of patients survive for up to 2 years [5].

Of the many chemotherapy agents that are clinically available, temozolomide (TMZ) is the only standard chemotherapy available to patients with GBM [6, 7]. TMZ is an oral alkylating agent that penetrates the brain and damages DNA by inducing DNA O^6^-methylguanine [8]. However, the expression of the DNA repair enzyme O^6^-methylguanine methyltransferase (MGMT) can abrogate the cytotoxic O^6^-methylguanine DNA adduct by repairing damaged DNA and thus contribute to drug resistance [9]. In addition, the overexpression of the ATP-binding cassette (ABC) efflux transporters, ABCG2 and ABCB1, provides chemoresistance by transporting drugs across the cell membrane into stem cells [10] and contributes to the blood–brain barrier (BBB) [11]. Therefore, the anti-tumor effect of TMZ monotherapy is constrained with limited clinical benefits. Most patients who are given TMZ monotherapy are unable to avoid tumor recurrence after surgery or drug resistance. There is a grave clinical problem that needs to be solved urgently regarding the limitations of TMZ monotherapy for patients with GBM in the absence of a broader range of broad-spectrum and effective chemotherapy drugs.

Levetiracetam (LEV), as an antiepileptic drug (AED), is mainly used for the treatment of partial seizures in adults and children with epilepsy over 4 years of age. In recent years, studies have found that levetiracetam was associated with a better survival rate when used in GBM patients [12–15]. Although these observational studies provide a compelling background for investigating the effect of LEV on GBM, the limitation of these studies stems from retrospective nature, including selection and information bias. On the other side, antiepileptic drugs used asynchronously with chemotherapy might underpower the potency of the anti-tumor effect of AEDs. It is not clear how LEV improves survival in patients with GBM. The potential antitumor activity of LEV might be due to the inhibition of MGMT transcription and expression in glioblastoma cell lines by increasing p53 binding on the MGMT promoter, thus sensitizing glioblastoma cells to the alkylating agent TMZ [16]. In addition, Scicchitano et al. reported that LEV enhances the effect of TMZ on proliferation and apoptosis in GBM cancer stem cells [17]. Furthermore, a study in vitro showed that the tumor-suppressing effect and the induction of cellular senescence of LEV are further enhanced when TMZ is combined with β-galactosidase activity [18]. The combination of TMZ and LEV is expected to offer complementary benefits and thus amplify the anti-tumor effect of TMZ.

Studies have demonstrated that the combination of LEV and TMZ is emerging as an optimal approach for improving the survival of GBM patients after surgery. It is therefore essential to conduct a prospective randomized controlled trial (RCT) to evaluate the effectiveness of TMZ plus LEV compared with TMZ standard chemotherapy. Seventy-three patients were enrolled in a Korean study (NCT02815410) that evaluated the effectiveness of LEV in GBM treatment. No differences were found in survival as a result of LEV. LEV had no significant side effects or overdose symptoms in the study, even when patients received an increased dose of up to 2000 mg/day and other AEDs as well [19]. However, the study was limited by a single-arm study design with external and historical control. In China, there is no correlative, randomized, and controlled trial that has been conducted to investigate the effects of LEV for GBM. As a result, we decided to conduct an RCT to explore the therapeutic effect of LEV plus TMZ for GBM, and thus provide an available therapeutic option for the treatment of GBM. The primary objective of this RCT is to determine whether the combination of TMZ and LEV is superior to standard TMZ chemotherapy in prolonging the progression-free survival (PFS) of GBM patients after surgery. This trial will also evaluate the efficacy of new chemotherapy regimens in improving the overall survival (OS), objective response rate (ORR), and the Karnofsky Performance status scale (KPS).

## Methods/design

### Study design

This is a prospective, single-center, randomized, double-blind, clinical trial to be conducted at the Second Affiliated Hospital of Chongqing Medical University in China. The study was registered with the Chinese Clinical Trial Registry on 14 August 2021 (ChiCTR-2100049941). The plan is to recruit 142 eligible subjects and assign them to either the control group (standard TMZ chemoradiotherapy) or the experimental group (TMZ plus LEV chemoradiotherapy) at a 1:1 ratio. Participants will undergo a 34-week treatment period and a 3-year follow-up period. The trial flow chart is shown in Fig. 1. The study protocol rigorously follows the Standard Protocol Items: Recommendations for Interventional Trials 2013 (SPIRIT 2013) checklist (see Additional file 1).

**Fig. 1 Fig1:**
[figure not shown]
The trial flow chart

### Outcomes

2.3.1 Primary outcome

The primary outcome is the PFS of patients, the time from randomization and group allocation to any recorded disease progression, and even death.

2.3.2 Secondary outcomes are as follows:
Overall survival (OS), the time from randomization and allocation to death for any reasonThe Karnofsky Performance status scale (KPS). The scale measures the levels of patient activity and medical needs. The score ranges from 100 (no signs of disease) to 0 (dead).Objective response rate (ORR) = (CR + PR)**/**total number of cases × 100%. A complete response (CR) is defined as the disappearance of all target lesions. A partial response (PR) is defined as a reduction of at least 30% in the sum of diameters of the target lesions, considering the baseline sum diameters as a reference. The ORR will be determined by MRI according to the Response Evaluation Citeria in Solid Tumors (RECIST) [20].Incidence of adverse events (AEs). Adverse events (CTC-Toxicity ≥ grade III) will be recorded and analyzed based on the Common Terminology Criteria for Adverse Events (CTC-AE) [21].

#### Other measures

Complete blood counts (CBC): ANC, platelet count; liver and renal function: serum creatinine clearance, total bilirubin level, aspartate aminotransferase (AST), and alanine aminotransferase (ALT)

### Interventions

The patients will be allocated to either the experimental group or the control group based on a blocked randomization sequence generated by SPSS 11 software for windows. A total of 34 weeks’ worth of medications will be prescribed to each group (including an interval of 4 weeks). The trial protocol was developed in accordance with the latest clinical standard care for GBM [22]. The standard of treatment for GBM patients who are under the age of 70 and have the good physical ability after maximal surgical resection currently consists of chemotherapy and radiation therapy (RT). Therefore, the interventions will be conducted according to the current clinical practice guidelines. A chart showing the administration of interventions is shown in Table 1.

**Table 1 Tab1:** A chart showing drug administration regimens

Treatment		Groups	
		Experimental group	Control group
**CCRT (6 weeks)**	RT	2.0Gy once daily, 5 days per week	
	TMZ	A daily dose of 75 mg/m^2^	
	LEV	500 mg, twice daily	Placebo tablets
**Adjuvant chemotherapy (6 cycles)**	TMZ	A daily dose of 100–200 mg/m^2^	
	LEV	200–1500 mg, twice daily	Placebo tablets

*Abbreviations*: *1 cycle*, 28 days; *RT*, Radiation therapy, *CCRT* Concurrent chemoradiotherapy

#### Concurrent chemoradiotherapy (CCRT)

##### Radiotherapy

Patients in both study arms will receive the same intensity-modulated radiation therapy (IMRT). The radiation dose will be 60Gy in 30 fractions without changing (2.0Gy once daily, 5 days per week for 6 weeks). The particular volumes of radiation treatment will be defined by clinical target volume (CTV) using MRI scan data.

##### Chemotherapy

During radiation therapy, TMZ will be administered orally to both groups at a dose of 75 mg/m^2^. A continuous use of this product would be permitted for 42 days if the non-hematological toxicity ≤ grade I (except for hair loss, nausea, and vomiting), according to the Common Toxicity Criteria (CTC) [21]. The product will be suspended if the following conditions are met: absolute white blood cell count ≥0.5 × 10^9^/L and < 1.5 × 10^9^/L, platelet count ≥10 × 10^9^/L and < 100 × 10^9^/L, and non-hematological toxicity class II. This product will be terminated if the following conditions occur: absolute white blood cell count < 0.5 × 10^9^/L, platelet counts < 10 × 10^9^/L, and non-hematological toxicity class III or IV.

In addition, patients in the experimental group will also receive LEV tablets for the same period of time. To prevent adverse reactions that may occur early in treatment [23], a lower dose will be administrated. The initial treatment dose is 500 mg twice daily for 42 days without any changes. During treatment, placebo tablets will be given to patients in the control group with the same dosage and appearance as LEV.

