#### Adjuvant chemotherapy

Four weeks after the end of the CCRT, six cycles of adjuvant therapy will be performed. Each 28-day cycle will begin with a daily dose of 150 mg/m^2^ of TMZ administered in the experimental group and control group. Starting with the second cycle, the dose of TMZ can be increased to 200 mg/m^2^. TMZ dose will be reduced to 100 mg/m^2^ at a daily dose if any of the following conditions are presented: absolute white blood cell count < 1 × 10^9^/L, platelet counts < 50 × 10^9^/L, and non-hematological toxicity class III. Moreover, this product will be terminated if non-hematological toxicity class III reappears or class IV reappears after the dose is reduced.

Based on the administration of TMZ, the dose of LEV in the experimental group will be adjusted to 1500 mg each time, twice a day, continuous for 6 cycles. The dosage of LEV will be adjusted according to renal function as follows: (1) mild abnormalities (creatinine clearance rate 50–79 mL/min): 750 mg, twice a day; (2) moderate abnormalities (creatinine clearance rate 30–49 mL/min): 500 mg, twice daily; and (3) severe abnormalities (creatinine clearance rate < 30 mL/min): 250 mg, twice daily. Increasing or decreasing the dosage by 500 mg/time every 2–4 weeks, twice daily, is recommended. During treatment, patients in the control group will be given placebo tablets with the same dosage and appearance as LEV.

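### The concurrent-phase temozolomide suspension and termination rules do not say whether their conditions apply singly or jointly, and neither reading fits cleanly with the 42-day continuation sentence

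*Protocol article*

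**What the plan says.** The protocol article, under Concurrent chemoradiotherapy (CCRT), Chemotherapy, gives three consecutive sentences on temozolomide.

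- **Continuation.** "A continuous use of this product would be permitted for 42 days if the non-hematological toxicity ≤ grade I". Hair loss, nausea and vomiting are excepted. No blood count appears in this sentence.
- **Suspension.** "The product will be suspended if the following conditions are met: absolute white blood cell count ≥0.5 × 10^9^/L and < 1.5 × 10^9^/L", followed by "platelet count ≥10 × 10^9^/L and < 100 × 10^9^/L, and non-hematological toxicity class II".
- **Termination.** "This product will be terminated if the following conditions occur: absolute white blood cell count < 0.5 × 10^9^/L, platelet counts < 10 × 10^9^/L, and non-hematological"; the last item is class III or IV toxicity.

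The suspension and termination lists each contain a white-cell item, a platelet item and a non-hematological toxicity class, with *and* before the last item. Neither list has *any of* in its lead-in.

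Under Adjuvant chemotherapy, a list of the same three kinds of item is introduced differently: "TMZ dose will be reduced to 100 mg/m^2^ at a daily dose if any of the following conditions are presented".

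**The concern.** The adjuvant-phase list states that one condition is enough; the two concurrent-phase lists do not. A reader who compares the sections could take the difference as deliberate and require all three conditions at once. A patient with a severe cytopenia and no other toxicity would then be neither suspended nor stopped, and the continuation sentence would allow dosing to go on.

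These are safety rules, applied to both arms during chemoradiotherapy. If staff follow the text literally, it gives no temozolomide instruction for isolated cytopenia. If they depart from it, nothing in the text ensures that they all do so in the same way. Temozolomide exposure, and the recording of adverse events of grade III or higher (a secondary outcome), could be affected.

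**Working it through.** The protocol gives no figure to reproduce. The check is one of logic, using the cut-offs in the Chemotherapy section. Each variable falls into three bands (counts × 10⁹/L):

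| Variable | Outside both lists | Suspension band | Termination band |
|---|---|---|---|
| White cells | ≥ 1.5 | 0.5 to < 1.5 | < 0.5 |
| Platelets | ≥ 100 | 10 to < 100 | < 10 |
| Non-hematological toxicity | ≤ I | II | III or IV |

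This gives 3 × 3 × 3 = 27 combinations, of which 27 − 1 = 26 have at least one abnormal item.

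**Reading 1: all three conditions required**
- Suspended: 1 × 1 × 1 = 1. Terminated: 1 × 1 × 1 = 1.
- Abnormal but meeting neither list: 26 − 2 = 24.
- Of these 24, toxicity ≤ grade I with an abnormal count: 3 × 3 − 1 = 8. The continuation sentence permits dosing in all 8. In 9 − 2 × 2 = 5 of them at least one count is in the termination band.
- The other 24 − 8 = 16 have toxicity of class II or higher and no stated action.
- Combinations where the continuation sentence contradicts a suspension or termination: 0. Continuation needs toxicity ≤ I, suspension needs II and termination needs III or IV, so they cannot coincide.

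Example: platelets 8, white cells 3.0, no non-hematological toxicity. Suspension is not met, because platelets are below its range and the other two items are normal. Termination is not met, because only one of three items holds. The continuation sentence is satisfied.

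**Reading 2: any one condition suffices**
- Meeting the termination list: 27 − 2³ = 19. Meeting the suspension list: 27 − 2³ = 19.
- Meeting both: 27 − 8 − 8 + 1 = 12. Termination only: 19 − 12 = 7. Suspension only: 19 − 12 = 7. Neither: 1. Check: 12 + 7 + 7 + 1 = 27.
- Toxicity ≤ grade I with an abnormal count: 8. Here the continuation sentence permits dosing while a following sentence suspends or terminates it.

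The two defects do not coexist. Reading 1 leaves isolated cytopenia without an instruction. Reading 2 supplies one, but sets the continuation sentence against the next two sentences and leaves 12 combinations under two different instructions.

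**Other parts of the protocol.** Blood counts are checked weekly (Adherence and concomitant care; During intervention). Severe events are reported promptly (Reports of adverse events). The withdrawal criteria include investigator judgement (Recruitment and eligibility criteria). None of these is a concurrent-phase temozolomide rule for cytopenia.

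**The case against.** The strongest reply is that the joint reading was never intended. The bands look like independent thresholds. The emergency unblinding criteria under Randomization and blinding have the same form, with a lead-in to the following criteria, no *any*, and *and* before the last item, yet they are plainly alternatives. The adjuvant-phase list itself uses *and* before its last item although it is headed *any of*. This stands: separate triggers are the likelier intent, and the problem is most likely one of drafting.

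It does not clear the section, because under that reading the continuation sentence still conflicts with the sentences after it. One can answer that it is a general permission, limited by the specific rules that follow, or only a necessary condition. Either is plausible, but the text says neither.

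It can also be said that weekly counts, event reporting, general adherence to practice guidelines and investigator discretion protect patients. They do, so the gap is the absence of a suspension or termination instruction in these sentences, not the absence of any response.

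Finally, the trial is single-center and blinded, with the same temozolomide rules in both arms. Differences between sites do not arise, and nothing shows an effect that differs between arms.

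**Conclusion.** The point holds as a defect in a stated safety rule. As worded, the section does not settle whether one condition or all three are needed. Read literally, it leaves isolated severe cytopenia without a suspension or termination. Read as separate triggers, it conflicts with its own continuation sentence in 8 of 27 combinations and meets both lists in 12, with no precedence given. Because the article prints the bands and the connecting words, this is not a detail left to a fuller document.

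A reader might infer more than the documents support:
- *That the trial means to keep dosing through isolated cytopenia.* The parallel wording of the unblinding criteria points the other way.
- *That the continuation sentence contradicts the other two on either reading.* Under the joint reading there are 0 contradictions.
- *That 24 of 26 abnormal states go without action in practice.* The combinations are counted equally, the protocol gives no patient frequencies, and the figure belongs to the joint reading only.
- *That separate triggers would terminate 19 combinations and suspend 7.* That split assumes termination overrides suspension, which the text does not say.

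The effect on exposure and on the adverse event outcome is possible but not shown.

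**What to change.** The sponsor should reconcile the three concurrent-phase sentences with each other and with the adjuvant-phase rule. The revised text should state:

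1. for the suspension list and for the termination list, whether the conditions apply singly or jointly;
2. which list prevails when a patient meets both;
3. how the 42-day permission relates to the blood-count rules.

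Which clinical rule applies is for the sponsor to decide; no threshold or dosing rule is proposed here. The cost is a few words in a protocol amendment and in any dosing instructions that staff use. Sample size and analysis are unaffected.

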### Reports of adverse events

Adverse events (AEs) will be assessed primarily by abnormal variations in laboratory data (including complete blood counts (CBC), liver function tests (total bilirubin level, AST, ALT), renal function tests (creatinine clearance, blood urea nitrogen), and clinical symptoms. The occurrence, severity level, management strategies, the causality related to the experimental agents, and the termination of all adverse events (AEs) will be recorded and preserved during clinical trials and follow-up. All severe adverse events (CTC-Toxicity ≥ grade3) will be reported promptly to the principal investigator and the research ethics committee (REC). The researchers and clinical trial institutions will ensure that the subjects are treated appropriately and informed truthfully of the relevant information. According to China’s Code of Quality Management for Drug Clinical Trials, researchers are responsible for the cost of dealing with adverse reactions and compensation for patients who suffer adverse reactions. Participants are not provided with specific post-trial care.

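### The levetiracetam dosing statements do not agree across the two treatment phases and Table 1, and the toxicity rules do not say how they apply to the blinded tablets

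*Protocol article*

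**What the plan says.** **Concurrent phase (Concurrent chemoradiotherapy, Chemotherapy).** The toxicity rules follow directly on the TMZ dose. Suspension: "The product will be suspended if the following conditions are met: absolute white blood cell count" and platelets lie in given bands, with class II non-hematological toxicity. Termination: "This product will be terminated if the following conditions occur", namely very low counts and class III or IV toxicity. For the test drug, "patients in the experimental group will also receive LEV tablets for the same period of time", and "The initial treatment dose is 500 mg twice daily for 42 days without any changes". The control group gets matching placebo.

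**Adjuvant phase (Adjuvant chemotherapy).** TMZ is reduced for low counts or class III toxicity, and ended if serious non-hematological toxicity returns after the reduction. For LEV, "the dose of LEV in the experimental group will be adjusted to 1500 mg each time, twice a day, continuous for 6 cycles". The same paragraph gives lower LEV doses for three bands of creatinine clearance, then adds: "Increasing or decreasing the dosage by 500 mg/time every 2–4 weeks, twice daily, is recommended".

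**Elsewhere.** Table 1 (Interventions) shows adjuvant LEV as a range from 200 to 1500 mg twice daily. Renal function is tested weekly during the intervention (Adherence and concomitant care; During intervention). Entry requires a creatinine clearance of at least 80 mL/min (Recruitment and eligibility criteria). Reports of adverse events lists creatinine clearance among the laboratory measures of adverse events, and has staff record "the causality related to the experimental agents".

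**The concern.** Site staff following this text would meet statements that cannot all be obeyed. A fall in renal function changes the LEV dose in one phase but may not change it in the other. The same paragraph supports both an immediate and a stepped rise to 1500 mg. The table permits a dose that the text never reaches.

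The toxicity rules raise a related problem. They act on TMZ without asking which drug caused the event, and say nothing about the LEV or placebo tablets. A patient who reacts to the test drug could lose standard chemotherapy, while the concurrent text allows no change to the drug responsible. What is at stake is patient safety, uniform handling of the blinded tablets, and knowing which regimen the trial actually tested.

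**Working it through.** The article states no figure to reproduce here, so the check sets the dosing statements side by side. The arithmetic is on doses and weeks only.

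**1. Renal function.** Inputs: the concurrent dose of 500 mg twice daily and the adjuvant renal bands.

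| Creatinine clearance (mL/min) | Concurrent text (mg/day) | Adjuvant text (mg/day) | Concurrent ÷ adjuvant |
|---|---|---|---|
| 50–79 | 2 × 500 = 1000 | 2 × 750 = 1500 | 0.67 |
| 30–49 | 1000 | 2 × 500 = 1000 | 1.0 |
| below 30 | 1000 | 2 × 250 = 500 | 2.0 |

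The concurrent dose exceeds the adjuvant dose only in the last row. To get there from the entry limit, a patient must lose more than 80 − 30 = 50 mL/min within six weeks, so few should be affected.

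**2. Rise to the adjuvant dose.** The default dose goes from 500 to 1500 mg, a ratio of 1500/500 = 3. In 500 mg steps this needs (1500 − 500)/500 = 2 steps. At 2–4 weeks per step, that is 2 × 2 = 4 to 2 × 4 = 8 weeks. The adjuvant phase lasts 6 × 28 days = 24 weeks, so the stepped reading puts 4/24 = 17% to 8/24 = 33% of it below the stated dose. The immediate reading puts none of it there. (If the first step falls on the first adjuvant day, one interval of 2–4 weeks remains; the text does not say.)

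**3. Table 1 range.** The text doses are 1500, 750, 500 and 250 mg, all multiples of 250, and the step is 500 mg. No combination of these gives 200 mg. The table's lower limit is 250 − 200 = 50 mg below the lowest dose in the text.

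**4. Which rule acts on which product.**

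| Trigger | TMZ | LEV/placebo |
|---|---|---|
| Grade or count, concurrent | suspend or terminate | none written |
| Grade or count, adjuvant | reduce or terminate | none written |
| Creatinine clearance, concurrent | none written | no change allowed |
| Creatinine clearance, adjuvant | none written | dose lowered |
| 500 mg step, adjuvant | not applicable | up or down, no trigger given |

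No grade or count rule refers to causality, although causality is recorded. No sentence says whether the blinded tablets are held, continued or stopped when TMZ is suspended or terminated.

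**The case against.** Several counter-arguments have force.

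- **LEV is not without dose rules.** A reader might infer that no safety rule touches LEV. The adjuvant section does lower it for creatinine clearance, which is itself an adverse-event measure, and it permits stepwise decreases. What stands is narrower: no rule triggered by grade or blood count is written for LEV, and the concurrent phase allows no change.
- **LEV need not continue after TMZ stops.** A reader might infer that it does. No sentence says so. Giving LEV over the same period as TMZ, and describing adjuvant LEV as based on TMZ administration, could be read as linking the two. Investigator-discretion withdrawal, emergency unblinding for severe adverse events and review by the data monitoring committee also exist. These are general safeguards, not LEV dose rules, so the handling remains unstated.
- **The concurrent conditions are joined by 'and'.** The adjuvant list says that any one condition suffices; the concurrent lists do not. Reading non-hematological toxicity alone as a concurrent trigger is natural, but it is an interpretation.
- **Different phases may have different rules.** That is true, and the renal doses conflict only below 30 mL/min. The article gives no reason why renal function should govern the dose in one phase and not in the other.
- **The step sentence may belong to the renal table.** The gaps there are 1500 − 750 = 750, 750 − 500 = 250 and 500 − 250 = 250 mg. None is a 500 mg step, so this reading does not settle the matter.
- **The trial result is not biased.** A reader might infer that TMZ lost to LEV toxicity biases PFS against the combination. Statistical analysis makes intention-to-treat the main analysis. Loss after randomization is part of the effect of assigning the combination, so it may dilute a pharmacological benefit without biasing that comparison. A power loss could be computed only by assuming an excess rate of TMZ loss, which the article does not give, and by borrowing its overall-survival medians for a trial whose primary outcome is PFS.
- **An article condenses the full protocol.** A missing LEV stopping rule alone would not be a finding. The point rests on statements that the article does make and that do not fit together.

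**Conclusion.** The point holds as a consistency and safety problem in the text, and it should be corrected.

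- **Renal statements:** a twofold difference in daily dose (1000 against 500 mg) below 30 mL/min, expected in few patients.
- **Rise to 1500 mg:** either immediate or about 4–8 weeks, assuming one full interval per step. This concerns every experimental patient on the default adjuvant dose.
- **Table 1:** a lower limit that no dose in the text reaches.
- **Toxicity rules:** as written, a reaction to LEV can cost a patient TMZ while the concurrent LEV dose may not be changed. This assumes that the concurrent conditions each suffice alone.

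The documents do not support a claim of bias in the intention-to-treat comparison. Any dilution of the treatment effect cannot be sized from them.

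**What to change.** Reconcile Table 1, the concurrent Chemotherapy section and the Adjuvant chemotherapy section so that the renal, step and range statements agree. In each phase, state how the toxicity rules apply to the blinded tablets and to TMZ, including what happens to the tablets when TMZ is suspended or terminated. Word this identically for LEV and placebo, so that it can be followed blinded in both arms. The sponsor's clinicians decide all doses, thresholds and rules; this review proposes none.

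The cost is a protocol amendment and a dose-modification entry in the CRF. Renal function is already tested weekly and causality already recorded, so no new visits or tests are needed. Depending on what the clinicians decide, some patients may receive less LEV than the nominal schedule.
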